## Abstract

**Background:**

Rheumatoid arthritis is a chronic inflammatory condition that affects the joints causing unpredictable episodes of pain, stiffness and disability. People with rheumatoid arthritis usually require lifelong specialist follow-up but frequently have periods when their disease can be managed through self-care or that provided by their general practitioner. Compared to the traditional clinician-driven care in rheumatoid arthritis, patient-initiated care has proven to be more beneficial in terms of reducing unnecessary medical reviews, providing greater satisfaction to patients and staffs and maintaining the patient’s physical and psychological status. We aim to evaluate the implementation of a patient-initiated review system in a routine secondary care rheumatology service in a public hospital in England, where patients get the opportunity to self-manage their disease by requesting specialist reviews at times of need instead of clinician-scheduled appointments.

**Methods/design:**

Three hundred and eighty patients attending routine review at Plymouth Hospitals NHS Trust will be randomised to either enrol immediately into a patient-initiated review system (direct access group), or to be seen regularly by a clinician at the hospital (regular clinician-initiated group). Patients (or their general practitioner) in the direct access group can arrange a review by calling a rheumatology nurse-led advice line that enables telephone delivered clinical advice, or where appropriate, an appointment with a rheumatologist within 10 working days. Patients in the regular clinician-initiated group will attend their planned appointments at regular intervals during the intervening period of 12 months. The primary outcome of interest is patient satisfaction; secondary outcomes include service use, waiting times and clinical measures. Semi-structured, in-depth interviews will be conducted with a subset of patients and staff with the aim of identifying facilitators/barriers in implementing patient-initiated clinics.

**Discussion:**

The implementation of a patient-initiated review system in routine care rheumatology will replace the fixed clinician-driven review system with a more flexible patient-driven system where patients usually self-manage their disease, but can request prompt help when required. We believe that this study will enable a comparison of the changes in local services and will be helpful in exploring the benefits/drawbacks of such implementation, thus providing lessons for implementation in other hospitals and for other chronic diseases.

## Background

Rheumatoid arthritis (RA) is a chronic disease that primarily affects the synovial joints causing unpredictable episodes of joint pain, stiffness and swelling. There are approximately 400,000 people with RA in the United Kingdom (UK), with around 15 men and 36 women developing RA per 100,000 people per year [1]. It has been estimated that the total cost associated with RA in the UK, including indirect costs and work-related disability is between £3.8 and £4.75 billion per year [1]. People with RA often have lifelong symptoms that fluctuate on a daily or longer basis, intermittent disease flares, and an unpredictable long-term outcome. Hence, these patients need to develop the skills to manage their own condition and its consequences on their lives [2].

In the UK, the majority of people with RA are managed by routine medical review initiated by the hospital rheumatologist or rheumatology specialist nurse every 3–6 months. However, this traditional system of review may lead to a mismatch between clinical need and clinical input. Patients are often seen on a date determined some time in advance, and review may occur when the patient is well rather than during periods of exacerbation [2]. A previous study into the content of routine reviews of patients with RA reported that 30% of routine appointments resulted in no investigations or other action; 35% were seen to be problem free; and 42% were thought to be unnecessary [3]. Hence, it is likely that considerable hospital out-patient time and resources are wasted on the one hand and on the other hand the systems of review may be unresponsive at the times when patients need them most.

A randomised controlled trial (RCT) conducted in Bristol, UK, compared traditional 3–6 monthly rheumatologist-initiated review with patient-initiated review alone [4-6]. This trial reported that patient-initiated reviews maintained the patient’s physical and psychological status but reduced unnecessary medical reviews by at least a third, thus making more efficient use of finite resources. The trial data also showed that patients and GPs had more confidence and satisfaction in such a system when compared to clinician- driven follow-up. Numerous studies looking at the impact of open access patient-initiated follow-up clinics in patients with medical conditions such as lung cancer [7], breast cancer [8], diabetes [9], urinary tract infections [10], gastroscopy [11] and endoscopy [12] have also reported positive effects resulting from such clinics in terms of patient care and satisfaction, cost-effectiveness and efficiency.

The National Institute for Health and Clinical Excellence (NICE) guidelines for RA recommend that people with satisfactorily controlled established RA should be able to review the frequency of their appointments at a location suitable to them and in addition, make sure they have access to additional visits for disease flares and know when and how to get rapid access to specialist care [1]. Similarly, The British Society for Rheumatology (BSR) guidelines state that patients need an individualised management plan including choices for long-term follow-up care, and self-initiated access to primary or secondary care including telephone advice [13]. These guidelines support the need for systems that promote self-management of care and treatment in patients with RA.

Given the evidence from the trial by Hewlett and colleagues [6], and the recommendations from NICE and BSR, we decided to implement a patient-initiated review system at Plymouth Hospitals NHS Trust (PHNT) in the UK. The Trust currently has a clinician-driven, overwhelmed and delayed outpatient follow up system for people with RA. We believe that the introduction of this evidence based review system will help to empower patients and provide them with the opportunity to self-manage the disease through the ability to request their own prompt specialist review when required.

## Methods

### Implementation process

Plymouth Hospitals NHS Trust serves a population of 460,000, and extrapolating from this figure it is estimated that there are about 4,500 patients with RA in the PHNT catchment area. Initially, all patients attending routine review at PHNT will be assessed for eligibility. People with RA who are 18 years or over, have had their disease for more than two years and are able to initiate telephone contact if needed will be deemed eligible. People will be excluded if they have no access to a telephone, or are thought unable themselves or through a relative or friend to initiate telephone contact via the advice line when their disease requires clinical review. All eligible patients will be educated about the patient-initiated review system prior to their enrolment into the system. However, due to the finite capacity of education sessions per week, all eligible patients will not be able to enroll into the system at once, and it will take more than twelve months to educate all the patients. Hence, we will use this timeframe as an opportunity to evaluate the new system of care against the comparator traditional clinician-driven system using a stepped-wedge study design. For this, a subgroup of patients suitable to have their care transferred to the patient-initiated review system will be randomised into two groups using computer generated numbers. The patients will either immediately enroll into the patient-initiated review system (Direct Access group (DA)), or will have regular clinician-initiated appointments (Regular Clinician initiated group (RC)) prior to transferring to the patient-initiated review system.

### Direct access group

After randomisation, people in the DA group will be provided with an initial information sheet explaining the system, and will be offered a choice of dates to attend a DA patient education session over the following weeks. The education sessions will comprise small groups of eight people with RA led by a rheumatology specialist nurse, and will focus on issues such as the operation of the DA system, what patients can expect from the system, when and how to call the advice line, when and how to ask for appointments, and any other queries regarding the system [2]. These patients will not be offered routine clinical review, and their GP will be informed about this and sent a short summary of managing common problems experienced by people with established RA. Patients or their GP can arrange prompt clinical advice and a review in clinic where required by calling a rheumatology nurse-led advice line where appointments can be accessed with a maximum delay of ten working days. The education session was piloted on fifty patients and following the feedback from the pilot session, changes were made before delivering it to the patients who are randomised. Any patients declining entry to the DA system will continue to have their care delivered through the traditional review system.

### Regular clinician initiated group

The RC group will receive planned appointments at regular intervals over the year prior to transferring to DA at the end of the 12 months implementation process (Figure 1). Patients in both groups who do not request an appointment or who do not attend a routinely scheduled medical appointment over 12 months will be contacted for a review by the rheumatology specialist nurse.

**Figure 1 F1:**
[figure not shown]
Flow diagram of the implementation trial study design.

### Implementation evaluation

The evaluation of the implementation process will be undertaken collaboratively between the PHNT Rheumatology Department and the Collaboration of Leadership and Applied Health Research and Care for the South West Peninsula (PenCLAHRC). The study will assess the following outcome measures.

### Primary outcome measure

#### Patient satisfaction

As a surrogate of service quality, patient satisfaction will be assessed at baseline and at the end of 12 months using the Short-Form Patient Satisfaction Questionnaire (PSQ-18) [14].

### Secondary outcome measures

#### Service use

Number of visits to the rheumatology consultant, rheumatology specialist nurse, physiotherapist and occupational therapist will be recorded over the period of 12 months. In a random sample of 50 patients (25 from each group), the cost of the total number of visits to hospital rheumatologists, visits to GPs and allied health professionals for problems related to arthritis and the associated travel costs will be calculated using NHS trust figures and published unit cost data [4].

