#### Waiting times

As the RC group will attend the clinician-initiated outpatient clinic at regular intervals; service availability upon request will be measured for the DA group only. Waiting time will be assessed by calculating the number of days from the advice line call to the medical appointment.

Semi-structured, in-depth interviews will be carried out with a subset of patients from both groups as well as with the health professionals and administrators involved in providing the service. Interviews will particularly focus on assessing barriers and facilitators of providing a patient-initiated service, reasons for implementation success/failure, psychological benefits/drawbacks and effects on wider life impacts, and perceived or real changes in the interaction between patients and the rheumatology team delivering their medical care. All the interviews will be recorded and later transcribed. Once all the transcripts have been analysed, a matrix will be designed which will enable the emergence of major themes and create an understanding of the individual and group coding. The interviews will add depth to the analysis of quantitative data and will be supplemented through the observation of a sample of patient education sessions given by a rheumatology specialist nurse. The observation of these sessions will allow us to gather first-hand information about the social processes between the specialist rheumatology nurse and patients in an educational context. This will help inform the semi-structured interviews as the qualitative researcher will have first-hand knowledge of how patients were educated about the new appointment system and what were their early thoughts about such process change.

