## Discussion

The implementation of the DA system in Plymouth will move the service provision from a traditional clinician-driven review system to a more flexible patient-driven system where patients can request help according to their needs. Our evaluation will provide routinely collected data enabling an assessment of the impact of implementing this type of service change in the National Health Service. In addition, the qualitative analysis will offer insights into the reasons why such a service implementation might be successful, and how both health staff and patients perceive both the benefits and drawbacks of such a change.

In the current evaluation we will be able to compare the changes in local services and inform local patients, commissioners and providers about the changes in rheumatology service provision. In the context of a previous RCT, the DA system was established as being more cost-effective, providing greater satisfaction to patients, GPs and rheumatologists, and reduced the delay in follow-up appointments compared with the traditional review system [6]. However RCTs cannot give evidence of how such a service change impacts on the delivery of healthcare in a routine setting. Our expectation is that this implementation of a patient-initiated system of care will reduce unnecessary appointments and costs, be more responsive to patients when they need rapid help, and through these processes empower patients to improve their own self-care. In the current financial climate it will be informative to see if these expectations are realised.

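### The cost comparison prices visits and travel but not the advice-line contacts or the education session on which Direct Access depends, so it is expected to favour Direct Access

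*Protocol article*

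**What the plan says.** The Protocol article (Secondary outcome measures, Service use) gives two lists.

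- Counted: "Number of visits to the rheumatology consultant, rheumatology specialist nurse, physiotherapist and occupational therapist will be recorded over the period of 12 months".
- Priced: "the cost of the total number of visits to hospital rheumatologists, visits to GPs and allied health professionals for problems related to arthritis", with travel added: "the associated travel costs will be calculated using NHS trust figures and published unit cost data". The costing sample is described as follows: "In a random sample of 50 patients (25 from each group".

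Other sections describe what DA consists of. The Abstract (Methods/design) has patients or their GP "calling a rheumatology nurse-led advice line that enables telephone delivered clinical advice", with an appointment given where that is appropriate. The Direct access group section withdraws routine review and makes this line the way to reach care. It also describes how patients enter the system: "The education sessions will comprise small groups of eight people with RA led by a rheumatology specialist nurse". According to the Regular clinician initiated group section, RC patients move to DA only at the end of the 12 months.

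Call data appear in one place, Waiting times, for DA patients only: "calculating the number of days from the advice line call to the medical appointment". The Discussion states the expectation that "implementation of a patient-initiated system of care will reduce unnecessary appointments and costs", and intends the results for commissioners and providers among others.

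**The concern.** DA replaces scheduled visits with telephone access to a specialist nurse, after a nurse-led group session. The cost comparison prices the visits that are removed. It does not price the telephone contact that takes their place or the session that patients attend to enter the system. Followed as written, it credits DA with each avoided visit and omits part of what it took to avoid it.

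What is at stake is the cost conclusion that the Discussion anticipates and that commissioners would use. A second, smaller issue concerns the visit count. If visits fall, that count alone cannot separate a fall in total contact from a move of contact to the telephone.

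**Working it through.** **1. The planned effect.** Inputs from Sample size and statistical analysis: 2.5 consultations a year in RC, 2.0 in DA, 5% significance, 90% power, 190 per group. With Poisson variance and a two-sided test:

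n per group = (1.960 + 1.282)² × (2.5 + 2.0) / 0.5² = 10.507 × 4.5 / 0.25 = 189.1, rounded up to 190.

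This reproduces the stated figure (a one-sided test would give 154.1). The planned saving is therefore 2.5 − 2.0 = 0.5 consultations per patient-year, and omitted inputs have to be judged against it.

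**2. What is counted and priced, set against what DA uses.**

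| Item | In the visit count? | In the cost list? | Arm that uses it during the 12 months |
|---|---|---|---|
| Rheumatologist visits | yes | yes | both |
| Allied health professional visits | yes (physiotherapist, occupational therapist) | yes | both |
| GP visits for arthritis | no | yes | both |
| Travel | not applicable | yes | both |
| Advice-line contacts | no | no | DA; RC access not stated |
| Group education session | not stated (could be read as a nurse visit) | no | DA only |

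The two items missing from the cost list belong mainly or wholly to DA. That gives the expected direction of the bias.

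**3. Break-even for calls.** The article gives no call rate or unit cost, so this step rests on assumptions. Let w be the cost of one call as a fraction of the full cost of a visit, including travel and clinic overhead. Let c be the extra calls per patient-year in DA over RC. The planned saving is cancelled when c × w = 0.5, so c = 0.5 / w.

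**4. Adding the session.** With groups of eight, each patient carries one eighth of a session. Assume a session takes the staff resource of one visit. The charge is then 1/8 = 0.125 visit per patient, before the patient's own travel, and break-even becomes c = (0.5 − 0.125) / w = 0.375 / w.

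| w (assumed) | Calls per patient-year that cancel the saving | Same, with the session charged |
|---|---|---|
| 0.10 | 5.0 | 3.75 |
| 0.25 | 2.0 | 1.5 |
| 0.50 | 1.0 | 0.75 |
| 1.00 | 0.5 | 0.375 |

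The last row treats a call as costing as much as a visit. It is an extreme, since a call is probably cheaper.

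**The case against.** **The article is condensed.** Two sentences on costing may stand for a fuller resource list elsewhere, and the text never says that calls are excluded. This would carry weight if the article were silent on what is priced. It is not silent: it names the priced items, and the result of those items is one-sided.

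**The visit count is not distorted.** This stands. The stated problem is unnecessary outpatient review, visits measure that directly, and a shift to the telephone is part of how DA is meant to work. A reader might infer that the visit outcome itself is biased; the documents do not support that. The primary outcome, patient satisfaction, is untouched.

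**The education session is a special case.** This stands in part. The session is led by the specialist nurse, so it may already be counted as a nurse visit. It is a one-off entry step and does not replace review. RC patients receive it later, and baseline clinical measures are taken at it. It is nevertheless a DA-only input in the comparison year and is not in the cost list. The Implementation process section names limited session capacity as the reason for phased enrolment, so it is not a free resource. A separate line for it is fair to both views.

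**RC patients may also use the line.** The article does not say. Such use would narrow the bias but would probably not reverse it.

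**Stronger claims about size.** A reader might reason that 190 DA patients with 2.0 consultations each must make at least 190 × 2.0 = 380 calls. That is not a lower bound. Follow-ups could be booked at a previous visit, and the article does not say whether a consultation includes telephone contact. A reader might also set nurse hours omitted against clinician hours saved. The article gives no durations or wages, and a comparison of time alone ignores the travel and clinic overhead that an avoided visit saves.

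**Conclusion.** The concern holds for the cost comparison. As specified, it omits advice-line contacts and the education session, and the DA minus RC cost difference is expected to favour DA. The direction rests on the design: routine review stops in DA, the line is the route to care and can settle a need by itself, and only DA patients are educated within the 12 months.

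The size cannot be computed from the article. Over assumed call costs of one tenth to one half of a visit, between 5 calls and 1 call per patient-year would cancel the planned saving. The omission could therefore be minor or could remove the saving. The documents do not show that DA costs more than RC, and that should not be inferred.

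The finding affects a secondary outcome measured in 50 patients, but it is the outcome that carries the cost conclusion.

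**What to change.** Amend Service use as follows.

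- **Count.** Record advice-line contacts per patient from the call log, in both arms if RC patients can use the line. Mark each as settled by telephone or as leading to an appointment, and report them in a row beside visits.
- **Price calls.** Include nurse telephone time in the cost comparison.
- **Price education separately.** Cost the session as nurse time divided by attendees, plus patient travel, on a one-off line apart from recurrent costs. Report the net DA minus RC cost with and without it.

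The cost is modest. Waiting times already needs dates for the calls that lead to an appointment. What is added is the calls settled by telephone, session attendance lists and two unit costs. No extra patients are needed. The downside is a little more data extraction, and the DA saving may look smaller.

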### Sample size and statistical analysis

The assumptions underlying the sample size calculation are derived from a published RCT [6]. In order to detect a decrease in the number of consultations from 2.5 per year in the RC group to 2 per year in the DA group at the 5% significance level with 90% power to detect this difference, we calculated that the current evaluation will require 190 subjects in each group followed up for a period of 12 months. Changes in other outcome measures between the two groups will be compared using simple tests of association such as chi-squared (*χ*^2^) test and Student’s *t*-test (depending on data properties). The qualitative data analysis technique described by Miles and Huberman [15] will be used to analyse the interview data. This means affixing codes to a set of field notes drawn from data collection and sorting through the material to identify relationships between themes. All interview recordings will be transcribed and checked for accuracy. The researcher will listen to the interview recordings and make comments on the transcript and read and re-read them to identify relevant codes. Once all transcripts have been analysed in this way a matrix will be designed which will enable the emergence of major themes and create an understanding of the individual and group coding. Computer aided software such as NVivo (a qualitative data analysis tool that helps to organise and analyse unstructured, i.e. non-numerical data) will be used to interrogate the data at different levels.

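### Costs and GP visits are measured in only 25 patients per group, too few to be likely to show the expected saving or to exclude a shift of work to GPs; recorded hospital contacts could be costed for everyone

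*Protocol article*

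**What the plan says.** The Service use section of the Protocol article makes two statements about resource use.

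- Hospital contacts: "Number of visits to the rheumatology consultant, rheumatology specialist nurse, physiotherapist and occupational therapist will be recorded over the period of 12 months". No subsample is mentioned.
- Costs: "In a random sample of 50 patients (25 from each group), the cost of the total number of visits to hospital rheumatologists" is to be calculated, along with "visits to GPs and allied health professionals for problems related to arthritis and the associated travel costs", from trust figures and published unit costs.

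GP visits appear only in the second statement. The article gives no reason and no target precision for 25 per group.

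Three other places bear on this:

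- The Abstract gives the trial size: "Three hundred and eighty patients attending routine review at Plymouth Hospitals NHS Trust will be randomised".
- The sample size section bases that size on consultations: "In order to detect a decrease in the number of consultations from 2.5 per year in the RC group to 2 per year", the lower figure being for DA. It arrives at 190 per group, with a 5% test and 90% power.
- The Discussion expects that the new system "will reduce unnecessary appointments and costs, be more responsive to patients when they need rapid help".

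Under Direct access group, routine review is withdrawn and "their GP will be informed about this and sent a short summary of managing common problems experienced by people with established RA".

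**The concern.** Lower cost is one of the stated expectations of the evaluation, and the results are meant to inform commissioners. Whether fewer hospital visits are a true saving depends on where the work goes. The DA arm loses routine review and its GPs receive guidance on common problems, so some transfer to general practice is plausible. The only data that could reveal it come from 50 of 380 patients (50/380 = 13%).

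A comparison of that size will most likely be inconclusive. A non-significant result could then be read as showing no cost difference or no added GP workload, when the interval would be compatible with a sizeable effect either way. Part of this imprecision is avoidable, because hospital contacts appear to be recorded for everyone and unit costs need no further data collection.

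**Working it through.** **Inputs.** From the sample size section: means of 2.5 (RC) and 2.0 (DA) consultations per year, difference 0.5 (20% of 2.5), 5% significance, 90% power, 190 per group. From Service use: 25 per group for costing. No SD is stated for visits, costs or GP contacts.

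**Step 1. Reproduce the planned size.** Assume Poisson counts (variance equal to the mean): SD = √((2.5 + 2.0)/2) = 1.5. Then n per group = 2 × SD² × (1.960 + 1.282)² / 0.5² = 189.1, rounded up to 190. This matches. A one-sided test would give 155, so the plan appears to be two-sided. Working backwards, 190 per group implies an SD of 1.503.

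**Step 2. Precision and power for a visit difference.** The standard error is SD × √(2/n). Power ≈ Φ(0.5/SE − 1.96).

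| | 25 per group | 190 per group |
|---|---|---|
| SE | 1.5 × √(2/25) = 0.424 | 1.5 × √(2/190) = 0.154 |
| 95% CI half-width (t quantile) | 2.011 × 0.424 = 0.85 | 1.966 × 0.154 = 0.30 |
| Power, normal approximation | 22% | 90% |
| Power, t-test | 21% | 90% |
| Difference detectable with 80% power, (1.960 + 0.842) × SE | 1.19 visits | 0.43 visits |

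A simulation of Poisson counts gave 21% and 90%. At 25 per group the half-width exceeds the 0.5 target, and the detectable difference is 1.19/2.5 = 48% of the RC mean. If visits vary more than Poisson, for example SD 2, t-test power at 25 per group falls to 14%.

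**Step 3. Costs.** The cost SD is unknown, so a range of coefficients of variation (CV) is assumed. SE as a fraction of mean cost is CV × √(2/n); half-widths use 1.96. A CV of 0.6 corresponds to the Poisson visit count (1.5/2.5).

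| Assumed CV | Power, 20% saving, 25 per group | Same, 190 per group | Power, one-third saving, 25 per group | 95% half-width, 25 per group | Same, 190 per group |
|---|---|---|---|---|---|
| 0.6 | 22% | 90% | 50% | ±33% | ±12% |
| 0.8 | 14% | 68% | 31% | ±44% | ±16% |
| 1.0 | 11% | 50% | 22% | ±55% | ±20% |
| 1.5 | 7% | 26% | 12% | ±83% | ±30% |

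**Step 4. Shift to GPs.** Suppose that the 0.5 hospital visits saved all reappear as GP visits. Assume Poisson GP counts with a base mean m of 1 to 4 per year: SD = √((2m + 0.5)/2), half-width = 1.96 × SD × √(2/n).

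| Base mean | Power, 25 per group | Half-width, 25 per group | Power, 190 per group | Half-width, 190 per group |
|---|---|---|---|---|
| 1 | 35% | ±0.62 | 99% | ±0.22 |
| 2 | 22% | ±0.83 | 90% | ±0.30 |
| 3 | 16% | ±1.00 | 77% | ±0.36 |
| 4 | 14% | ±1.14 | 66% | ±0.41 |

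At 25 per group every half-width exceeds 0.5. Even if the observed difference in GP visits were zero, the interval would still include complete one-for-one transfer.

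**The case against.** The strongest reply is that the hospital side of the question is not lost. Hospital contacts are recorded with no stated limit, the trial is sized on consultations, and the visit difference has about 90% power in the full sample. Unit costs are close to fixed multipliers, so a reader could price that difference. This stands. A reader might infer that the plan throws away the data of the other 330 patients, or that it cannot show a saving at all. The article supports neither reading: the visits are kept as an outcome, and power of about 21% is low but not zero.

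It is also fair that GP visits and travel need extra data collection, that a subsample is a common economy for such items, and that a condensed article may omit the reason for choosing 50. This justifies a subsample for those items. It does not explain why contacts already recorded for everyone should be costed in only 13% of them.

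Cost is a secondary element with no stated target saving, and nothing in the article commits the authors to a conclusion of no difference. The risk is therefore one of interpretation. The general analysis sentence plans between-group tests for other outcomes, however, and the costing is not marked as descriptive. As for a shift to GPs, the article says only that GPs are informed and sent a summary, and it also lets them call the advice line. The shift is plausible but not shown.

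**Conclusion.** The point holds in limited form. Total cost and GP use will be estimated too imprecisely at 25 per group to be likely to show the expected saving or to exclude a shift to primary care. Power is about 21% for the planning difference in visits, 22% to 7% for a 20% cost saving, and 35% to 14% for a 0.5-visit rise in GP contacts. The primary outcome and the full-sample comparison of hospital visits are untouched.

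The visit figures rest on a Poisson SD inferred from the planned size. The cost CVs and GP means are assumptions shown as ranges; power is low across all of them, apart from reaching 50% for a one-third saving at the smallest CV. That hospital contacts exist for all 380 is inferred from the absence of any limit in Service use.

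A reader might also infer that a full-sample hospital cost could replace the planned costing. It should not: it leaves out GP visits and travel and would flatter DA if work moves to GPs.

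**What to change.** 1. Apply unit costs to the recorded hospital contacts of all randomised patients. Report the mean difference with a bootstrap 95% CI, labelled as hospital cost only. This costs analysis time and no new data collection.
2. Keep the 50-patient sample for GP and travel costs. Report it as descriptive, with confidence intervals, and state in advance that it will support no conclusion of no cost difference or of no increase in GP use. This costs only wording.
3. Optionally, add an item on the number of arthritis-related GP visits to the 12-month questionnaire for all patients, and include it in a total-cost analysis. This costs one question. Patients know which system they are in, so recall error over 12 months may differ between groups; check the answers against records in the 50-patient sample.
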